## Abstract

**Background and objective:**

Sedentary behavior is of increasing concern in older patients with type 2 diabetes mellitus (T2DM) due to its potential adverse effects on cardiovascular health, cognitive function, and motor function. While regular exercise has been shown to improve the health of individuals with T2DM, the most effective exercise program for elderly sedentary patients with T2DM remains unclear. Therefore, the objective of this study was to assess the impact of high-intensity interval training (HIIT), moderate-intensity continuous training (MICT), and guideline-based physical activity programs on the cardiovascular health, cognitive function, and motor function of this specific population.

**Methods:**

This study will be a randomized, assessor-blind, three-arm controlled trial. A total of 330 (1:1:1) elderly sedentary patients diagnosed with T2DM will be randomly assigned the HIIT group (10 × 1-min at 85–95% peak HR, intersperse with 1-min active recovery at 60–70% peak HR), MICT (35 min at 65–75% peak HR), and guideline-based group (guideline group) for 12 weeks training. Participants in the guideline group will receive 1-time advice and weekly remote supervision through smartphones. The primary outcomes will be the change in glycosylated hemoglobin (HbA1c) and brain-derived neurotrophic factor (BDNF) after 12-weeks. Secondary outcomes will includes physical activity levels, anthropometric parameters (weight, waist circumference, hip circumference, and body mass index), physical measurements (fat percentage, muscle percentage, and fitness rate), cardiorespiratory fitness indicators (blood pressure, heart rate, vital capacity, and maximum oxygen), biochemical markers (high-density lipoprotein, low-density lipoprotein, triglycerides, total cholesterol, and HbA1c), inflammation level (C-reactive protein), cognitive function (reaction time and dual-task gait test performance), and motor function (static balance, dynamic balance, single-task gait test performance, and grip strength) after 12 weeks.

**Discussion:**

The objective of this study is to evaluate the effect of 12 weeks of HIIT, MICT, and a guideline-based physical activity program on elderly sedentary patients diagnosed with T2DM. Our hypothesis is that both HIIT and MICT will yield improvements in glucose control, cognitive function, cardiopulmonary function, metabolite levels, motor function, and physical fitness compared to the guideline group. Additionally, we anticipate that HIIT will lead to greater benefits in these areas. The findings from this study will provide valuable insights into the selection of appropriate exercise regimens for elderly sedentary individuals with T2DM.

**Ethics and dissemination:**

This study has been approved by the Ethics Review Committee of the Reproductive Hospital Affiliated with China Medical University (approval number: 202203). Informed consent will be obtained from all participants or their guardians. Upon completion, the authors will submit their findings to a peer-reviewed journal or academic conference for publication.

**Clinical trial registration:**

Chinese Clinical Trial Registry, identifier ChiCTR2200061573.

## Introduction

Worldwide, population aging has led to a rise in the number of elderly individuals living with chronic illnesses. Among these illnesses, type 2 diabetes mellitus (T2DM) is a prevalent metabolic condition, with prevalence rates projected to double in the next three decades, posing substantial medical and economic risks (Cho et al., 2018). Furthermore, T2DM often coexists with cardiovascular disease (CVD), with a staggering eight out of ten T2DM patients succumbing to CVD-related complications (Laakso, 2001). In addition to cardiovascular risks, individuals with T2DM may also experience a decline in motor and cognitive function (Chohan et al., 2021; Farup et al., 2021). They exhibit worse performance in terms of standing balance and walking speed, rendering them more susceptible to falls (Morrison et al., 2012; Volpato et al., 2012). Moreover, the behavior of patients could be affected by diseases, and sedentary behavior is becoming increasingly common. Elderly individuals are more likely to exhibit a sedentary lifestyle, which significantly contributes to the rising prevalence of T2DM (Farup et al., 2021). A sedentary lifestyle can result in various adverse effects, such as a decline in cardiopulmonary fitness (Chohan et al., 2021), elevated cardiovascular risk, cognitive decline, and impaired motor function (Morrison et al., 2012). Consequently, the combination of a sedentary lifestyle and advanced age increases the susceptibility of T2DM patients to concurrent cardiovascular impairment and cognitive and motor dysfunction.

Numerous non-pharmacological interventions (diet manipulation, exercise, etc.) have been used for the prevention and management of type 2 diabetes. Regular exercise is widely recognized as an effective strategy for both the prevention and management of T2DM (Volpato et al., 2012). The World Health Organization 2020 guidelines on physical activity and sedentary behavior provide an overview of exercise that is beneficial for elderly individuals and suggest moderate-intensity continuous training (MICT) at least 3 days a week (World Health Organization, 2020). Substantial evidence from clinical and experimental research shows that MICT has a variety of benefits in patients with T2DM, including protection of cardiovascular health, improvement of cognitive function and fall prevention (Morrison et al., 2014; Chiang et al., 2019). Moreover, there is a growing body of evidence suggesting that high-intensity interval training (HIIT) presents a time-efficient alternative to MICT. The interaction between exercise intensity and duration plays a pivotal role in eliciting distinct adaptations, but the optimal model for exercise remains uncertain. Therefore, comparing HIIT and MICT is crucial in the context of T2DM rehabilitation. Research has indicated that HIIT yields comparable, if not superior, cardiovascular benefits for individuals with T2DM. However, importantly, the available evidence regarding its efficacy in elderly sedentary patients with T2DM is still limited (de Mello et al., 2022; Li et al., 2022). Furthermore, there are insufficient data to draw definitive conclusions about the impact of HIIT and MICT on cognitive and motor function in this specific population. While HIIT holds promise as an alternative to MICT, particularly in terms of cardiovascular benefits, its application and suitability for elderly sedentary patients with T2DM require further investigation. Additionally, more research is needed to fully understand the effects of both exercise modalities on cognitive and motor function in this specific population. Such investigations will provide valuable insights into optimizing exercise prescriptions for individuals with T2DM, promoting their overall wellbeing and functional capacity.

Therefore, we designed a single-blind randomized controlled trial to analyze the effects of HIIT, MICT, and guideline-based physical activity on cognitive function, motor function, cardiovascular health, and metabolic markers in sedentary elderly patients with T2DM.

## Materials and methods

### Research design

This study is a randomized, assessor-blind, three-arm, superiority, parallel controlled trial. Participants will be randomly assigned to the HIIT group, MICT group, or guideline group. Testing will be performed at baseline and after the 12-week intervention. The minimum attendance rate will be established in light of the least beneficial dose of exercise. According to previous research (Abreu et al., 2021), participants who complete fewer than 24 training sessions will be considered to drop out of the study. All health and fitness tests will be conducted using the same equipment at the different testing sites. All blood samples will be measured by the same type of facility, and all blood samples will be stored in the Experimental Center of China Medical University for subsequent analysis. An overview of the trial procedures is displayed in Figure 1. This study was approved by the Ethics Review Committee of the Reproductive Hospital Affiliated to China Medical University (approval no. 202203, China clinical trial registration number: ChiCTR2200061573^1^). All patients will provide written informed consent prior to enrollment, and the results of the study will be reported following the Consolidated Standards of Reporting Trials (CONSORT) guidelines.

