### Intervention

All patients will be advised (50 min seminar) on the health benefit of exercise according to current guidelines before intervention. We report our intervention according to the TIDieR checklist. After the informed consent and screening steps are completed, patients will be randomly assigned to three groups (in a 1:1:1 ratio): the MICT group, involving moderate-intensity continuous training (MICT); the HIIT group, involving high-intensity interval training (HIIT); and the guideline group, involving guideline-based physical activity (Figure 1). Participant compliance is of paramount importance for this study, and every possible measure will be taken to maintain adherence to the exercise intervention and follow-up plans. If a participant fails to attend three consecutive sessions, the researcher will actively inquire about the reasons for their absence and provide encouragement for continued participation. To account for the minimal effective dose of exercise, a minimum attendance rate has been established based on previous research findings (Abreu et al., 2021). Specifically, participants who complete fewer than 24 training sessions will be classified as dropouts. The adherence to the training program will be meticulously monitored and regularly documented throughout the trial, allowing for comprehensive analysis and evaluation. Reasons for terminating the test: if serious adverse events occur during exercise, the test should be terminated in time. Adverse events: (1) severe hypoglycemia and complications: shaking, dizziness, abnormal sweating, headache, blurred vision, (2) chest pain, arrhythmia, (3) breathing difficulties and asthma.

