#### Guideline group

Participants in the guideline group will perform 1-time supervised 40–50 min of dedicated training (including jogging and brisk walking) 3 times a week in addition to daily physical activity, and the rate of perceived exertion (RPE) will be set at 3–4 (Borg RPE scale: 12–16). Afterward, WeChat–a mobile-based messaging App (Tencent cop., China)- will be used to remotely monitor and supervise exercise weekly. The exercise data (intensity and duration) will be collected weekly to ensure sufficient exercise time and to encourage exercise motivation.

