#### HIIT group

Participants will perform training with supervision, involving walking on a flat or inclined treadmill 3 times a week. The HIIT protocol consists of a 10-min warm-up (at 50–60% of the peak HR), 10 × 1-min intervals at 85–95% of the peak HR separated by 1-min periods of active recovery (at 60–70% of the peak HR), and a final 5-min cooldown, which corresponds to the Borg RPE scale of 16–17. An HR monitor (Polar Electro, Kempele, Finland) will be used to obtain the training HR. The speed and incline of the treadmill will be continuously adjusted to ensure that each training session is performed at the prescribed HR.

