#### MICT group

Similar to the HIIT group, the participants in the MICT group will perform training with supervision, involving walking on a flat or inclined treadmill 3 times a week. Corresponding to the amount of exercise (exercise intensity × duration) of the HIIT sessions, each MICT session will consist of a 5-min warm-up period and a 5-min cooldown period at 30% of the peak HR, separated by 35 min of exercise at 65–75% of the peak HR. An HR monitor (Polar Electro, Kempele, Finland) will be used to obtain the training HR. The speed and incline of the treadmill will be continuously adjusted to ensure that each training session is performed at the prescribed HR.

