### Statistical analysis

The intention-to-treat principle will be employed for all analyses, ensuring that participants are analyzed according to their assigned treatment groups. Linear mixed models will be utilized, incorporating participant and baseline values as random effects, to estimate changes within groups (with a difference between groups of *P* < 0.1) for all outcome measures. To address missing data, the multiple-imputation method will be employed to test its influence on the analysis. All statistical analyses will be conducted using R software (version 4.0.2, the R Project for Statistical Computing^2^). The hypothesis tests will be two-sided, and statistical significance will be defined as *p* < 0.05. For the primary outcomes, multiple will be not necessary as the α value have been allocation in the sample calculation. Importantly, no adjustments for multiple comparisons will be made for secondary outcomes, and therefore, their interpretation should be considered exploratory in nature. Subgroup analyses based on sex, duration of T2DM, and BMI will also be performed to examine potential variations within these subgroups. A per-protocol sensitivity analysis will be applied.

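### The 24-session rule turns low attenders into dropouts from the study and is not reconciled with the intention-to-treat analysis

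*Protocol article*

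**What the plan says.** The rule appears twice in the protocol article. Under Research design, "participants who complete fewer than 24 training sessions will be considered to drop out of the study". Under Intervention, "participants who complete fewer than 24 training sessions will be classified as dropouts". Both places link the threshold to a minimum useful dose of exercise, and neither limits it to particular arms.

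The Statistical analysis section states: "The intention-to-treat principle will be employed for all analyses, ensuring that participants are analyzed according to their assigned treatment groups". On missing values it adds: "To address missing data, the multiple-imputation method will be employed to test its influence on the analysis". It ends its list of analyses with: "A per-protocol sensitivity analysis will be applied". The per-protocol set is not defined there, and the 24-session threshold is not mentioned.

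Sessions are observed differently across arms. For HIIT: "Participants will perform training with supervision, involving walking on a flat or inclined treadmill 3 times a week". For MICT, "the participants in the MICT group will perform training with supervision, involving walking on a flat or inclined treadmill 3 times a week". In the guideline arm, training is also described as three times a week, but after the start a messaging app "will be used to remotely monitor and supervise exercise weekly". The weekly data named for that arm are intensity and duration, not a session count.

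The Sample size calculation section enlarges enrolment for a 20% dropout rate. Research design and Measurements give two assessment times: baseline and after 12 weeks.

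**The concern.** Attendance is something that happens after randomization and is partly a result of the programme assigned. Under intention-to-treat it can describe how well a participant adhered, but it cannot decide who has left the trial. The plan uses the word for leaving, and its sample size section uses the same word for the people it allows for losing.

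Two people following the article could therefore act differently. A site worker could reasonably close the file of someone with 20 sessions and not call them for the final blood sample. The analyst would need that sample. With no outcome between baseline and week 12, a participant missed at week 12 leaves nothing after baseline to work from. Any model or imputation would then rest largely on participants of the same arm who were measured, mostly attenders.

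Both primary outcomes, HbA1c and BDNF, depend on this visit. Research setting says recruitment is still under way, and a week-12 sample that was not taken cannot be obtained later.

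**Working it through.** **1. The threshold.** Three sessions a week for 12 weeks is 3 × 12 = 36 planned sessions, and 24/36 = 66.7%. A participant who attends up to 23 of 36 sessions (64%) is a dropout under the rule.

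**2. The sections side by side.**

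| Question | Research design / Intervention | Statistical analysis |
|---|---|---|
| Status below 24 sessions | Has dropped out | Not mentioned; all analysed as assigned |
| Week-12 tests for them? | Not stated | Needed for the analysis |
| Excluded from the primary analysis? | Not stated | No, if intention-to-treat is applied |
| Threshold tied to the per-protocol set? | No | No |

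No sentence excludes these participants from the analysis, and none protects their follow-up.

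**3. Possible size if low attenders are lost.** From Sample size calculation: HbA1c difference 0.2, SD 0.3, dropout 20%. Assumptions: 20% of an exercise arm fall below 24 sessions, the 0.20 holds for attenders, low attenders get a fraction f of that benefit, and the comparator mean is unaffected.

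Difference in all randomized = 0.20 × (0.8 + 0.2f)

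- f = 0: 0.16. Attenders only: 0.20. Ratio 0.20/0.16 = 1.25, a 25% overstatement.
- f = 0.5: 0.18. Ratio 0.20/0.18 = 1.11, an 11% overstatement.

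**4. Dependence on both arms.** Let q1 and q0 be the shares removed in the exercise and comparator arms. Let g be how much worse, in SDs, the removed do than those kept, taken as the same in both arms. Shift = (q1 − q0) × g × 0.3.

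| q1 | q0 | g | Shift in HbA1c, % | As share of 0.2 |
|---|---|---|---|---|
| 0.2 | 0.2 | any | 0 | 0 |
| 0.2 | 0.1 | 0.25 | 0.0075 | about 4% |
| 0.2 | 0 | 0.5 | 0.03 | 15% |
| 0.2 | 0 | 1.0 | 0.06 | 30% |
| 0.1 | 0.2 | 0.5 | −0.015 | −7.5% |

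The last row shows that the sign reverses when the comparator loses more people. The f = 0 case in step 3 corresponds to q1 = 0.2, q0 = 0, g = 0.20/0.3 = 0.667, a shift of 0.04. That is 20% of 0.20 but 25% of 0.16, so the percentages in steps 3 and 4 have different bases.

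**5. Power if everyone is kept.** One-sided 0.025 split equally between two outcomes is 0.0125. With 110 per arm, SE = 0.3 × √(2/110) = 0.0405 and 0.16/0.0405 = 3.96. The noncentral t gives 95.5%. Mixing responders and non-responders adds 0.8 × 0.2 × 0.20² = 0.0064 to the variance of the exercise arm. Then SE = √((0.0964 + 0.09)/110) = 0.0412, the ratio is 3.89, and power is Φ(3.89 − 2.24), about 95%. With a difference of 0.18 and SD 0.3, power is 98.5%. At 0.00625, a stricter level that the plan does not state, the figures for 0.16 and 0.18 are 92.4% and 97.3% (SD 0.3).

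For 90% power at 0.16 and one-sided 0.0125, 89 measured per arm are enough (SD 0.3). So 110 − 89 = 21 per arm (19%) could still be truly missing.

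The point has no stated figure of its own to reproduce. The 110 per arm is larger than the stated inputs require (58 per arm at 90% power and 0.0125; 58/0.8 gives 73). That is a separate matter, but it explains why the dilution is affordable.

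**The case against.** The strongest reply is that the article attaches a label and nothing more. Statistical analysis says all analyses follow intention-to-treat by assigned group. Measurements says participants are assessed again after 12 weeks, with no attendance condition. A person can be called a dropout and still be measured and analysed. A minimum dose of exercise is a typical per-protocol criterion, a per-protocol analysis is planned, and a condensed article may leave the definition of analysis sets to a fuller document. Multiple imputation is described as a check of influence, and no imputation model is given.

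Most of this stands. It rules out the stronger reading that a reader might infer, namely that the plan removes non-adherers from the primary analysis or imputes them from attenders. Neither is written.

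A reader might also infer that the rule cannot be applied in the guideline arm. The documents do not support that either: exercise data are collected weekly there, and the Intervention section promises that adherence is documented throughout the trial. What remains is narrower. The remote record is less direct than supervised attendance, and no session count is named for that arm.

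The reply does not remove the conflict in wording. Both statements of the rule speak of dropping out, one of them from the study itself, and nothing ties the threshold to the per-protocol set. This is a rule that is stated and badly fixed, not a detail left out.

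**Conclusion.** The point holds as an unreconciled conflict between the dropout rule and the intention-to-treat commitment. It does not hold as a demonstrated exclusion or a demonstrated bias. The harm is conditional: it arises only if low attenders are not measured at week 12 or are left out of the primary analysis.

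If that happened to 20% of an exercise arm, with the comparator mean unaffected, the HbA1c difference would be overstated by about 11% at half benefit and 25% at none. The 25% should not be read as the expected bias. It needs every participant below 24 sessions, even one with 23, to gain nothing, and it takes the whole 20% dropout allowance to be low attenders, although the plan does not say what that allowance contains. Equal removal with equal prognosis gives no shift, and heavier removal in the comparator reverses the sign. A bias in favour of HIIT or MICT is therefore possible but not established.

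The correction is still worth making now, because it is cheap and missed final samples cannot be recovered.

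**What to change.** - In Research design and Intervention, call participants with fewer than 24 sessions *non-adherent* instead of dropouts.
- State that every randomized participant is invited to the week-12 assessment and kept in the primary intention-to-treat analysis, whatever the attendance.
- Reserve *dropout* for withdrawal of consent or absence of a week-12 measurement.
- In Statistical analysis, use the 24-session threshold only to define the per-protocol sensitivity set. Say that guideline-arm sessions are counted from the weekly remote record, and note that this count is less direct than supervised attendance.

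The cost is a change of wording, plus calling some non-adherent participants back for a visit already in the schedule. The primary effect may look slightly smaller. Under the assumptions above, power stays above the planned 90%.

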**FIGURE 1 F1:**
[figure not shown]
Flowchart of participant recruitment and study procedures. Eligible subjects will be randomly assigned to the HIIT group, the MICT group, or the guideline group and evaluated at two time points. HIIT, high-intensity interval training; MICT, moderate-intensity continuous training.

### Research setting

We will recruit 330 eligible T2DM participants from 3 communities in Shenyang by posters, leaflets and brochures and by conducting health seminars; community physicians will be involved in participant recruitment. All diagnostic participants will be evaluated by clinicians. The exercise interventions and measurements of anthropometric parameters and physiological indicators will be performed at community exercise clinics. The research staff who blinded to group allocation will collect baseline data, supervise the training, and finish outcomes related test in clinical exercise physiology. Participants was initial enrolled in June 2022 and the recruitment is still undergoing.

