### Random assignment and blinding

After the baseline assessment, we will randomly assign the participants into three equal groups (1:1:1), namely, the HIIT group, MICT group, and guideline group. This study is an assessor-blind randomized controlled trial, and indicators will be measured at baseline and after 12 weeks by assessors blinded to group allocation. Study interventions will be delivered by study staff. A randomization table will be provided by the Department of Statistics, School of Public Health, Fudan University (Excel software; Microsoft). Study staff who blinded to the group allocation will collect the measurements and maintain possession of the randomization table. The group allocation of participants will be recorded on a paper in an opaque envelope that will only be opened after the baseline assessment of participants has been completed.

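### Community is not named in the stated outcome model, so any difference between the three communities in 12-week change would cost some precision, though not validity

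*Protocol article*

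**What the plan says.** Research setting: "We will recruit 330 eligible T2DM participants from 3 communities in Shenyang". The same section says that the exercise sessions and the body and physiological measurements "will be performed at community exercise clinics".

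Research design acknowledges several sites and standardises some things across them: "All health and fitness tests will be conducted using the same equipment at the different testing sites". For blood, the promise is "All blood samples will be measured by the same type of facility", with storage in one centre.

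Random assignment and blinding describes individual 1:1:1 allocation. "A randomization table will be provided by the Department of Statistics"; no strata are mentioned.

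Statistical analysis gives one model for all outcome measures: "Linear mixed models will be utilized, incorporating participant and baseline values as random effects". Community is not named. Sex, diabetes duration and BMI are named, but for subgroup analyses.

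**The concern.** Community is a structural feature of this design: it determines where a participant is recruited and trained, and where part of the testing is done. Baseline adjustment removes much of any stable difference in level between communities. It does not remove a difference in how much participants change over 12 weeks, which could arise if supervision, adherence support or usual diabetes care vary locally.

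Neither usual safeguard, stratified allocation or a model term, is mentioned. Any such difference would be counted as residual error and would widen the confidence intervals. This applies to HbA1c and BDNF, and perhaps more to the secondary outcomes measured at the clinics, for which no power is stated.

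**Working it through.** **Inputs from the article (Sample size calculation).** 330 participants, 110 per arm; HbA1c difference in change 0.2% with SD 0.3%; 20% dropout, so 110 × 0.8 = 88 completers per arm; one-sided α of 0.025 split equally over two outcomes, so 0.0125 each (z = 2.241).

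**Assumed, because the article gives no figure.** Three communities of equal size with equally spaced mean changes; a range R of 0.1, 0.2 or 0.3% between the highest and the lowest after baseline adjustment; 0.3% taken as the within-community SD. There is no community-related figure in the plan to reproduce.

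**1. Variance between communities.** Means at −R/2, 0 and +R/2 have variance 2(R/2)²/3 = R²/6.

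**2. Effect of adjustment.** Under unstratified individual randomisation, the ratio of adjusted to unadjusted variance of an arm difference is about 0.09/(0.09 + R²/6). The unadjusted sample giving the same precision as 330 adjusted participants is 330 divided by that ratio.

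| R | R²/6 | Variance ratio | Cut | Equivalent extra participants |
|---|---|---|---|---|
| 0.1% | 0.00167 | 0.982 | 2% | 330/0.982 − 330 ≈ 6 |
| 0.2% | 0.00667 | 0.931 | 7% | 330/0.931 − 330 ≈ 24 |
| 0.3% | 0.01500 | 0.857 | 14% | 330/0.857 − 330 = 55 |

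**3. Power for HbA1c with community omitted.** With no community variance, the SE is 0.3 × √(2/88) = 0.045 and power is Φ(0.2/0.0452 − 2.241) = Φ(2.18) = 98.5%. The largest range above corresponds to a community share of 0.015/0.105 = 14% of the variance. At a still larger assumed share of 20%, the total SD is 0.3/√0.8 = 0.335, the SE is 0.0506, and power is Φ(0.2/0.0506 − 2.241) = Φ(1.71) = 95.7%. The number needed for 90% power rises from 56 to 70 per arm, still below 88.

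**4. If 0.3% is instead the total SD.** The planned SD then already contains the community variance, and omitting the term costs nothing against the plan. Including it would raise power from 98.5% to 98.6%, 98.9%, 99.2% or 99.7% for assumed shares of 1%, 5%, 10% or 20%.

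**5. Chance imbalance.** With fixed totals of 110 per arm and 110 per community, the count in one arm and community has mean 36.7 and SD √(110 × 1/3 × 2/3 × 220/329) = 4.0. At a 20% share and a total SD of 0.3%, with 88 completers per arm, imbalance contributes an SD of √(2 × 0.20 × 0.09/88) = 0.020 to the arm difference. That is part of the 0.045 above, not an addition to it.

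**6. Type I error with community omitted.** In simulation (20,000 trials per setting, unstratified allocation), the rejection rate was 0.0128, 0.0127 and 0.0125 for shares of 0, 5% and 20%, against a nominal 0.0125.

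**The case against.** The strongest objection is that this argues from silence. A reader might infer that the model contains only participant and baseline. The article does not say so: the sentence lists random effects and leaves out even treatment arm, without which no comparison could be estimated, so it is not a complete list of terms. A condensed article may also leave covariates and strata to fuller documents. This stands, and it is why the point is a suggestion for the stated model and not an error in it.

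A reader might also infer that staff and local care do differ between communities. That is plausible but not stated. The article points partly the other way: common equipment, training set by heart-rate targets, and central blood storage. Both primary outcomes are blood assays, so testing at the clinics bears on them less, although a shared type of facility is not a promise of one laboratory.

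Third, the larger assumed ranges are generous. A range of 0.2% equals the whole planned MICT-versus-guideline effect, and 0.3% is 1.5 times it, between communities of one city. At 0.1% the gain is about 2%. This too stands, and the true gain may be near zero.

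What survives is that the term is cheap, suits the design whether or not the list was stratified, and is best fixed in advance, since adding it later would look data-driven. If the list was in fact stratified, leaving the stratum out makes the standard errors too large.

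**Conclusion.** The point holds as a low-severity, optional gain in precision. The stated model does not name community, and no stratification by it is mentioned. The gain is about 2% to 14% of the variance of an arm difference, or roughly 6 to 55 participants on 330. It depends entirely on the assumed range of 0.1 to 0.3% in HbA1c change, on equal and equally spaced communities, and on 0.3% being the within-community SD.

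A reader might conclude that the primary comparisons would be biased or their error rate inflated. The design does not support that: participants are randomised individually, chance imbalance is ordinary sampling error already reflected in the standard error, and the simulated type I error holds. Nor is the primary HbA1c test endangered at the planned effect, with power above 95% even at a 20% community share.

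**What to change.** Add community (three levels, fixed effect) to the model under Statistical analysis, for all outcomes, and record this before outcome data are seen. The calculation above takes 12-week change, or the 12-week value adjusted for baseline, as the response; if both visits are kept as responses, the term has to be community by visit to do the same work. It would also help to state whether the allocation list was stratified by community.

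The cost is 2 degrees of freedom, and a negligible gain if communities do not differ.

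Leave the randomisation list unchanged. Recruitment began in June 2022 and is described as continuing. Switching to blocks within communities now would mix two allocation schemes and could make assignments easier to predict in a trial where only assessors are blinded and study staff hold the table.
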